## Randomization

The children aged 4–6 years within four classes (two classes selected from K2 and K3 grade, separately) will be randomized from the designated kindergartens using Research Randomizer software. The preschoolers in each class who meet the eligibility criteria will be screened by the kindergarten teachers and staff. To avoid changes in teachers and classmates affecting the results of this course, we will intervene in the form of a nature class. In total, 12 nature classes in grades K2 and K3 from the 3 kindergartens will be assigned to a PE curriculum in their respective schools, that is, 4 classes in the sport-featured kindergarten with “Hello sunshine” PE curriculum, the OPE group will have ordinary PE classes, the PE class in the FP group will be free play. This sequence will then be concealed in an opaque envelope.

## Blinding

Trained graduate students and senior undergraduate students will act as researcher. The researcher will not know which children will have had which intervention until the end of the study. However, each of the participants will know which group he/she is belongs to. Thus, only single blind (blind the researcher) will be applied in this study. The data will be renamed and converted into statistics by the second author.

### Interventions

In the study, the participants will be divided into three groups. The PE teacher will use various kinds of ball game-based curriculum in the HS group. The OPE group will have the ordinary preschool PE class that uses the kindergarten-based syllabus with a PE teacher (ball skills are not the main teaching contents). The FP group will play freely in outdoor activities with no guidance from teacher. The three groups will have the same daily life at kindergarten, except for the content of the PE class and outdoor time. PE classes will be 25 or 30 min, one or two times per week (depending on the student grade). Outdoor time will be implemented for 30 min per day, 5 days a week for 10 weeks during the intervention period. All three methods (HS, PE, and FP) are believed to improve motor skills and physical activity. The differences in the three methods are described below. This description follows the Template for Intervention Description and Replication checklist and guidelines for better reporting of interventions (Hoffmann *et al.*, 2014).

#### HS group

The HS project’s design is based on the physical literacy framework (Whitehead, 2013). It is a well-structured, age-demarcated, PE curriculum that includes five modules: knowledge, motor skills, physical quality, psychological quality, and health behavior. Each module has different course objectives and content in accordance with age. The HS curriculum consists mainly of ball skills activities including teaching or practicing ball skills in PE class, ball club time, and autonomous regional area in outdoor time. It consists of nine kinds of ball activities, such as football, basketball, badminton, table tennis, baseball, golf, handball, bowling, and snooker. K2 students will have a PE class (one ball topic for 25 min) and a ball clubs’ class (children volunteer to join any club for 60 min) once a week. In addition, they will have one football activity (autonomous regional play) in the afternoon outdoor time, daily. K3 children will have PE class (football or basketball) twice a week and ball club activities once a week, and football topic activity two times and golf topic activity in outdoor activity time once. In the PE class, ball game-related general knowledge, ball skills, and so on will be taught. In ball clubs’ time, children will participate and practice in ball games with the PE teacher. During outdoor activity, children will play in an autonomous regional ball area with supervision by the vice-class teacher for 30min.

An experienced PE teacher will teach basic ball skills in the context of a game or story and motivate the children to complete the task, while also enjoying themselves. The teacher will guide the children through the preset game scenarios, while demonstrating and explaining basic ball skills and their task or activity execution via prompt words that remain consistent with the teaching plan. Timely encouragement and feedback will also be provided to the children. During the outdoor class, high-autonomy interventions, wherein the children have the freedom to self-navigate through a ball skills game station are to be conducted.

Taking K3 for example, size 3 footballs or size 4 basketballs will be used during the nature classes to help the children learn and practice in the PE class. Hoops, traffic cones, disk cones, inclined plates, and mini-goals will be used as teaching aids. Participants will undergo 30-min classes, including jogging and playing games for a warm-up of 5–8 min, followed by 20 min of learning ball skills (PE class) or playing ball activities (outdoor times), and finally, 2–5 min of cooldown (using the ball to stretch and lightly pat themselves along with music). The teachers will monitor the intensity of play by observation of facial expression and color, and respiratory rate as recommended by the physical activity guidelines for Chinese preschool (Working Group on Physical Activity Guideline for Chinese Preschoolers Aged 3–6 Years, 2020) and assist children to engage in energetic play (NHS GGC, 2017; WHO Team, 2019).

#### OPE group

Children will have PE class with the PE teacher according to the assigned kindergarten textbook (Hainan edition) for monthly theme teaching, not focused on ball skills. K2 and K3 will have one PE class in the afternoon, five times/week and the same outdoor time as the HS group, but structured as FP.

#### FP group (control group)

The kindergarten will have a space for children to play freely with all kinds of sports equipment (slide, sand, climbing frame, etc.) They will be supervised by vice-class teachers without PE backgrounds.

## Fidelity

The fidelity measurements of the HS and OPE interventions are based on the curriculum lesson plan and curriculum summary provided by kindergarten teachers, which record the theme, goal, design, and other contents of the course. Research group experts will attend one class per week in each kindergarten at random to check that reporting from teachers accurately reflects the activities delivered.

### Outcome measures

The assessment process will use a variety of methodologies (scales, field tests, questionnaires, and ability-based tasks) and multiple informants (teachers and parents). An overview of the measurement process is shown in Table 1.

**Table 1. tbl1:** Domains and factors measured by the tests

Domain	measure	Items	Tools
Primary outcome			
Physical development	Anthropometrics	Hight Weight	Hight and weight scale
	Physical fitness	Strength Balance Agility Flexibility	Tennis throwing test Standing long jump Walking on a balance beam 10-m SRT Sit and reach
Motor development	Movement assessment	FMS	TGMD-3
Cognitive development	Cognitive self-regulation	Cognitive self-regulation	HTKS
Social development	Social competence	Emotional competence	SCEB-30 (teacher)
Secondary outcome			
Personal	Basic information	Perceived motor competence	PMCS-TGMD-3
		Temperament	CBQ-VSF (parents)
Family environment	Basic information	Parents’ age Parents’ education Physical activity and home play spaces	Questionnaire (parental report)
	Basic information	Sports injure Attendance rate	Recorded by teacher
Epidemiology	Recorded information		Recorded by school doctor

#### Anthropometric measures

The height and weight of the children will be measured in the morning by the research assistants. The children will wear light clothing, without shoes, and their standing height and body weight will then be measured using an electronic scale. Body mass index will be calculated as weight/height squared (kg/m^2^), and the weight status will be classified by Chinese preschooler overweight and obesity criteria (Li *et al.*, 2010).

#### Physical fitness measures

We will choose items from the National Physical Fitness Measurement Standards Manual (State Sport General Administration, 2003). Tennis ball throwing, sitting, and reaching tasks represent aspects of health-related fitness (muscle strength, flexibility) and standing long jump, walking on a balance beam, and the 10-m SRT test represent skill-related physical fitness (explosive strength, balance, and agility).

#### Movement measures

##### Gross motor skills

FMS will be assessed using [name] of Gross Motor Development-3 (TGMD-3) (2019), a validated and reliable assessment tool for measuring gross motor skill competence in children aged 3–10 years (Dale A, Ulrich, 2013; Brian *et al.*, 2018). The TGMD-3 is subdivided into two subscales: locomotor (running, galloping, 1-legged hopping, skipping, jumping, and sliding) and ball skills (2-hand striking, 1-hand striking, dribbling, kicking, catching, overhand throw, and underhand throw). Each skill is evaluated based on three to five performance criteria. If a child demonstrates the correct performance criteria, a score of 1 for each criterion is given; otherwise, they receive a score of 0. Children complete one practice and then two formal trials. Coding is only completed for the two formal trials, which are summed to calculate the raw score.

#### Cognition measures

##### Cognitive self-regulation

Executive function (EF) is used to describe “higher or meta” cognitive function (Miyake *et al.*, 2000) and is critically important in the overall neuropsychological functioning of the developing child (Isquith *et al.*, 2005). The Head–Toes–Knees–Shoulders (HTKS) test (Ponitz *et al.*, 2009; Meador *et al.*, 2013) assesses children’s behavioral self-regulation, which reflects their ability to transform executive functioning into explicit behaviors (Becker *et al.*, 2014), including a measure of inhibitory control, working memory, and attention focusing (Ponitz *et al.*, 2008). The test has strong interrater reliability and is a good evaluator of the behavioral self-regulation of children aged 4–8 years from different cultural backgrounds (Ponitz *et al.*, 2008). The test is divided into two parts. The first task is Head to Toes (HTT) and the child is required to react in the opposite way to two oral instructions from the examiner (when the child hears “touch your head” they should respond by touching their toes, and vice versa). The child will perform six practice trials with feedback followed by 10 test trials. If the child passes the HTT section, they will complete an advanced task, which mixes the knee and shoulder commands. In this task, the child should respond to the new commands (“touch your shoulders” and “touch your knees”) by performing the opposite action and touch their knees or touch their shoulders, respectively. This section concludes with 10 test trials that mix touch your head or shoulders, knees or toes oral prompts. HTKS is composed of 26 irregular instructions (16 trials of HTT and 10 trials of HTKS). Children get 2 points for correct responses, 0 points for incorrect responses, and if they immediately correct a wrong action, they score 1 point. Thus, the score range is 0 to 52 points (Meador *et al.*, 2013). This test was previously used in the study of Chinese preschool children (Ma *et al.*, 2019).

## Social competence

Emotional ability is crucial to building interpersonal relationships (Parke, 1994). Even during the preschool period, emotional competence contributes to social competency and has long-term implications (Denham *et al.*, 2003).

## Emotional competence measure

The shortened version of the Social Competence and Behavior Evaluation Scale (SCEB-30) (LaFreniere and Dumas, 1996) will be used for measuring participants’ emotional competency levels and will be utilized in each class with the classroom teacher. The test consists of three subscales: social competence, anger aggression, and anxious-withdrawal. It has high interrater and test–retest reliability, internal consistency, and over 6-month temporal stability (LaFreniere and Dumas, 1996). The Chinese revised version has proven to have good reliability and validity when applied for Chinese preschoolers (Liu *et al.*, 2012).

### Covariate and mediator

#### Personal factors

Age will be calculated as the children’s month-based ages, as it is going to affect the intervention’s outcome. Participants’ perceived motor competence will be measured with a pictorial scale for perceived movement skill competence (PMSC) that builds upon the TGMD-2 (Barnett *et al.*, 2015). It consists of 13 pictures illustrating cartoon boys (boy version) or girls (girl version) performing TGMD-3 skills. It shows middle to high instrument reliability and face validity in Chinese children (Diao *et al.*, 2018). Children will be shown illustrations by the examiner and judge whether the cartoon character is good at doing the skills, then choose between four Likert scale options (1 to 4, from “not too good” to “really good”).

Individual temperaments are expected to be predictive of the differential effects of this motor skills intervention (Taunton *et al.*, 2018), and they will be assessed using the 36-item Children’s Behavioral Questionnaire-Very Short Form (CBQ-VSF) (Putnam and Rothbart 2006). The test is divided into three broad dimensions: surgency, negative affect, and effortful control and it demonstrates acceptable internal consistency. It is a very short form based on the well-established parent report measure of temperament CBQ questionnaire for children aged 3 to 8 years (Rothbart *et al.*, 2001) and it has medium to high reliability and validity confirmed by studies in multiple countries. The CBQ-VSF provides moderate reliability of scale scores for assessing temperamental characteristics in preschoolers (de la Osa *et al.*, 2014).

#### Family factors

Parents of the participants will fill out questionnaires to provide additional information about their sociocultural characteristics. For example, occupational status will be defined according to the following categories ranging from low to high: unemployed, worker, education and teaching, self-employed, management, executive position, and professional (Vandendriessche *et al.*, 2012) and education level will be classified from low to high level: 1) secondary school or less, 2) trade certificate/diploma, and 3) university qualification (Hacke *et al.*, 2019). Family income will not be asked for privacy reasons.

#### Environment factors

##### Parental report of physical activity

Children’s physical activities promote the development of their FMS (Fisher *et al.*, 2005; Stodden *et al.*, 2008). Parental reports of their preschool-aged children’s physical activity levels are feasible in studying the home (available recreational space inside the home) and environment (community) of population-based samples (Burdette *et al.*, 2004).Our survey will explore this factor using self-designed parent reports of physical activity based on Palou’s (2019) study. The parents will be asked to answer the following questions:“Your children’s physical activity time every day after school is …?” The response options are 1 = 30 min or less, 2 = between 30 min and 1 h, 3 = between 1 h and 2 h, 4 = between 2 h and 3 h, 5 = more than 3 h.“Your children’s screen time after school is …? The options are: 1 = less than 30 min, 2 = between 30 min and 1 h, 3 = between 1 h and 2 h, 4 = between 2 h and 3 h, 5 = more than 3 h. (WHO Team, 2019; Working Group on Physical Activity Guideline for Chinese Preschoolers Aged 3–6 Years, 2020).“How many times do you perform moderate or vigorous exercise for at least 30 min per week ….?” Optional answers are: 1 = 0 times, 2 = 1 to 2 times, 3 = 3 to 4 times, 4 = 5–6 times, 5 = more than 6 times (Li *et al.*, 2020; WHO 2020).“How much space in your house for child recreational play?” The size options are: 1= < 20 m^2^, 2 = 20 to 50 m^2^, and 3 = > 50m^2^ (Bardid *et al.*, 2013).“How often is your child allowed to play in the community playground or sports facilities ?” Optional answers are 0 = never, 1 = during weekends, 2 = every now, and 3 = nearly daily (Niemistö *et al.*, 2020).

### Study procedure

After conducting the preliminary research work, the researchers will contact three kinds of kindergartens in this district and communicate with the directors to enquire whether they are interested in research on the health benefits of physical activity in young children. It was agreed that once the study has been approved by the ethics committee, the researchers will recruit participants from selected kindergartens. The kindergartens will send invitations to parents, along with information about the project and an informed consent form. After the collection of the signed consent forms, eligible participants will be screened by the kindergarten teachers, and the researchers. The baseline measurements will be conducted in the initial 2 weeks and all the participants will experience the same assessment at the end of the 10 weeks intervention. The experimental process will be administered as shown in the flow diagram (Figure 2). The physical fitness test, TGMD-3 test, and psychological test (PMCS and HTKS) tasks will be tested in random order in each kindergarten and based on their schedules and space availabilities both at baseline and after 10 weeks intervention, should finish within 4 days in each kindergarten with trained research students responsible for grouping the test items. All children will be encouraged with snacks or stickers to complete all tests. Video recordings will be used for later scoring and checking. The participants will be given a separate and quiet space to take the psychological test. Parents will receive their digital-based questionnaires at a parents’ meeting. They will fill these out and submit them on the day. The head teacher of each class will fill in the SCEB-30 questionnaire in 1 week.

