### Methods and design

#### Study design

A quasi-experimental design study will be employed.

At the beginning of the September 2021 school semester, preparations and baseline data collection will be carried out over 2 weeks, with an intervention period running for 10 weeks. This will be followed by a posttest period and a 6-week follow-up. At the beginning of the February 2022 semester, the third round of testing will be conducted. Given the uncertainty of the pandemic, if the school temporarily closes again, the project will be postponed until the next semester or the next opportune time.

This study’s procedures are illustrated in Figure 2.

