## Participants

The study will be conducted in three types of kindergartens in the center of Haikou city, China. Sport-featured kindergartens, public kindergartens, and inclusive private kindergartens in the same district will be assigned. Two classes in K2–K3 grade (children aged 4–6 years) will be randomly selected from these kindergartens and will be allocated as HS group (from sport-featured kindergarten), OPE group (from public kindergarten), and FP group (from inclusive private kindergarten).

The inclusion criteria are: 1) healthy and typically developing children willing to participate, 2) aged 4–6 years, 3) with the informed consent of their primary caregivers, 4) the primary caregiver must have a smartphone to answer the questionnaire. Children 1) who have difficulty in communication, unexplained health problem, 2) who have a contraindication to exercise such as congenital heart disease, asthma, fever, malaise, diarrhea, and 3) who have additional training from a sports club will be excluded.

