## Results

Data will be imported from Excel 2019 to IBM SPSS version 26.0 for inferential statistical analysis. The normal distribution of the data will be checked before determining the descriptive statistics for all variables (means and standard deviations). The participants’ basic information will be descriptive, including age, gender, and BMI. The primary outcomes will be expressed as continuous. If data are approximately normal distribution, the effect of the PE curriculum intervention on dependent variable (FMS, or TGMD, or HTKS, or SCEB score) will be investigated with repeated ANOVAs within factor: time (pre and post), between factors: group (HS, OPE, and FP) and gender (boy and female) and Bonferroni post hoc tests. Further, the relationship between FMS and other domains will be identified by regression analysis. Finally, the potential influence of individual factors (such as age, gender, and temperament) on the intervention effect will be investigated by comparing the gain in FMS score and subscale. Multiple regression equation is used to further explore the extent to which social-ecological factors contribute to the FMS score level at baseline. Statistical significance will be set at *P* < 0.05.

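### The pre–post repeated ANOVA uses only children with both scores, and because each arm is one kindergarten, missed tests may fall on one arm; a mixed model with catch-up testing is the better choice

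*Protocol article*

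**What the plan says.** **Analysis.** The Results section names SPSS 26 and specifies "repeated ANOVAs within factor: time (pre and post), between factors: group (HS, OPE, and FP) and gender (boy and female"), with Bonferroni post hoc tests, separately by outcome. Time has two levels. The February 2022 round described under Study design is not one of them.

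**Testing.** Under Study procedure, the fitness tests, TGMD-3, perceived-competence scale and HTKS "should finish within 4 days in each kindergarten with trained research students responsible for grouping the test items", at baseline and after the 10 weeks. Baseline as a whole is longer: "The baseline measurements will be conducted in the initial 2 weeks". The teacher-rated SCEB-30 is collected separately over one week.

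**Arms.** Under Participants and Randomization, each arm is one kindergarten with four classes.

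**Allowance.** Sample size determination gives at least 249 children, 83 per group, after a 5% inflation for non-inclusion.

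**Illness.** One exclusion criterion under Participants covers children "who have a contraindication to exercise such as congenital heart disease, asthma, fever, malaise, diarrhea". Table 1 shows that attendance is recorded by the teacher and epidemiology by the school doctor.

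**The concern.** A standard two-time-point repeated ANOVA is an analysis of within-child change. For a given outcome, a child without the pre or the post score contributes nothing, even though the other score is on file. This follows from a method that the article commits to, not from silence about missing data.

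The design makes the consequence less benign than usual. The children are aged 4–6, testing is planned for a few days per site, and arm and site coincide. A local outbreak around a test round would therefore hit one arm. If it fell mainly on one class, it would also fall on one grade, and so on one age band of that arm. The gains being compared would then come from differently selected children. The authors themselves expect weather and COVID-19 to affect delivery and compliance (Strengths and limitations).

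**Working it through.** **Inputs from the protocol article:** 83 per group, 249 in total, 12 classes, 5% inflation, 5% significance, 80% power, time = pre and post. **Not given:** effect size, SD, absence rate, pre–post correlation. Values used for these below are assumptions or back-solved.

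**1. The plan's own figure.** 249 cannot be derived without an effect size; only the inflation can be checked. 78/(1 − 0.05) = 82.1, rounded up to 83; alternatively 79 × 1.05 = 82.95, again 83. The uninflated requirement was therefore probably 78 or 79 per group. For a two-sided two-group comparison, 78 per group implies a standardised difference of √(2/78) × (1.960 + 0.842) = 0.449.

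**2. What the 5% covers.** If a proportion *a* is missing at each round independently, complete pairs are (1 − a)². Setting this to 0.95 gives a = 1 − √0.95 = 2.5%.

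| Missing per round (assumed) | Complete pairs | Per group | Power at 0.449, clustering ignored |
|---|---|---|---|
| 2.5% | 95.1% | 78.9 | 80.4% |
| 5% | 90.3% | 74.9 | 78.4% |
| 10% | 81.0% | 67.2 | 73.9% |

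At 5% per round about 24 of 249 children drop out of an outcome's analysis, nearly all (23.7) with one score on file.

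**3. How far a second chance helps.** If *a* is instead the chance of missing one test slot, and each child has two independent chances per round, the loss is 1 − (1 − a²)². At a = 5% this is 0.5% rather than 9.8%; at a = 10% it is 2.0% rather than 19%. Illness lasting several days would put the truth between these figures.

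**4. One class.** 83/4 is about 21 children, a quarter of an arm.

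**5. Bias.** Simulation: 4,000 runs, 83 per group, no true effect, baseline complete, pre–post correlation ρ of 0.5 or 0.7.

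- *Post score missing at random in both arms:* no bias. At 10% missing and ρ = 0.5 the standard error is 0.164 for complete pairs and 0.163 for a likelihood analysis.
- *Missingness in one arm rising as baseline falls* (logistic, slope 1 per SD; the nominal rate is that of a child at the mean baseline, so the average rates in that arm are about 13% and 24%):

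| Nominal loss | ρ | Complete pairs, shift (SD) | Likelihood, shift (SD) |
|---|---|---|---|
| 10% | 0.5 | −0.059 | 0.000 |
| 10% | 0.7 | −0.031 | 0.005 |
| 20% | 0.5 | −0.105 | −0.002 |
| 20% | 0.7 | −0.062 | −0.001 |

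A direct check agrees. The expected shift is (ρ − 1) times the mean baseline of the retained children, which is 0.119 SD at nominal 10% and 0.204 SD at 20%. With ρ = 0.5 that gives −0.060 and −0.102; with ρ = 0.7, −0.036 and −0.061.

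**The case against.** Several stronger readings are tempting, and the text does not support them.

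- *The 4 days close a round.* The wording is a target fitted to each site's schedule and space. It sits within a 2-week baseline and a separate posttest period, and does not forbid catch-up testing.
- *Acute illness removes enrolled children.* The criterion governs eligibility at screening. A child kept out there may have no scores to lose.
- *A child missing any round is lost altogether.* Loss is per outcome. SCEB-30 does not depend on the 4 days, baseline FMS scores still enter the baseline regression, and missing only February 2022 removes nobody from the ANOVA.
- *The loss will be 6–19% and exceed the allowance.* That assumes one slot per round and absence rates that the article does not give.
- *The article lacks a missing-data policy.* That is commonly left to the full protocol or SAP and is no finding here.

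Study design also provides for postponement if the school closes, which answers full closure but not an outbreak short of it.

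The strongest objection is that complete pairs do little harm if loss is random, and nothing shows that illness selects on motor or cognitive scores. That stands, and it limits the point to a conditional one. It does not justify keeping a method that is exposed when an equally simple one is not.

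**Conclusion.** The point holds in a limited form. For fitness, TGMD-3 and HTKS, the stated ANOVA discards any child lacking the pre or post score, and the design allows that loss to fall on one arm. The 5% allowance is not worded for loss after enrolment and would in any case cover only about 2.5% per round under independence.

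The size of any harm cannot be established from the documents. It is negligible as bias if loss is random. Under the assumed baseline-dependent loss in one arm it is about 0.03–0.06 SD at a nominal 10% and 0.06–0.11 SD at 20%, that is, up to roughly a quarter of the back-solved 0.449 (0.105/0.449 = 0.23). A likelihood analysis removes that shift when missingness depends only on observed scores. It does not restore the power lost to missing tests, and it does not repair loss that depends on unobserved scores. Only completing the tests does that.

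**What to change.** 1. **Analysis (Results section).** Replace the repeated ANOVA with a likelihood-based mixed model with time, group, gender and their interactions as already planned, and an unstructured pre–post covariance. Include every enrolled child's observed scores, by kindergarten group. SPSS can fit it. With complete data it gives the same group-by-time estimate, so nothing is lost.
2. **Testing (Study procedure).** Use the remaining days of the 2-week baseline period for catch-up testing by the existing testers, and set a post-test period of equal length in all three kindergartens. Record each child's test date. The cost is a few extra sessions and slightly more spread in test dates.
3. **Reporting.** Give missed tests and reasons by arm, from the attendance and school-doctor records already kept.
4. **Clarification (Participants).** The criterion lists fever, malaise and diarrhea beside lasting conditions. The sponsor should say whether these exclude a child or only defer testing; no rule is proposed here.

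None of this addresses the confounding of arm with kindergarten, which is a separate matter.
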